#### Inoculation

Eligible consenting volunteers who are not already naturally colonised with *N. lactamica* will receive nasal inoculation with 10^5^ CFU *N*. *lactamica* Y92-1009, using a sterile pipette (0.5 mL inoculum per nostril).

### Postpartum follow-up

Mother–neonate pairs will be reviewed 1 day, 1 week and 1 month post partum. At each visit, maternal consent for neonatal sampling will be re-affirmed, and respiratory samples will be collected (table 2). An optional umbilical cord blood sample (visit 3) and neonatal venous blood sample (visit 5) will be collected, as well as relevant clinical data (including mode of delivery, infant feeding and use of antimicrobials). Optional breastmilk samples will also be collected at each postpartum visit (up to 5 mL each at visits 3 to 5). Volunteers may decline optional blood and breastmilk sampling without affecting their enrolment in or completion of the rest of the study.

Volunteers’ experiences of participation (including acceptability and tolerability of inoculation and maternal and infant sampling) will be captured using optional questionnaires, to help us identify areas for improving volunteer experience in current and future studies.

### Optional visit 6 (15+/−2 weeks post partum)

At the time of writing, a study amendment is in progress to include an optional study visit at 15±2 weeks post partum (visit 6). This visit will involve maternal and infant pharyngeal, saliva and venous blood sampling, as well as saliva and oropharyngeal swabs from household contacts under 5 years old. In a recent *N. lactamica* controlled human infection study involving non-pregnant adults, anti-*N. lactamica* immunoglobulin G (IgG) (peak titre and titre increment) correlated inversely with subsequent pharyngeal colonisation density at 28 days post-inoculation (unpublished data), suggesting that IgG may play a role in controlling *N. lactamica* carriage. Total IgG is up to 1.5 times more concentrated in umbilical cord blood compared with maternal blood,^23^ and the half-life of transplacental maternal IgG is approximately 30 days^24^; thus, infant anti-*N. lactamica* IgG is predicted to be less than 10%–20% that of maternal IgG by 15±2 weeks (3 to 4 half-lives). Visit 6 therefore offers a valuable opportunity to investigate the association between anti-*N. lactamica* IgG and *N. lactamica* carriage in mother–infant pairs.

### Sample processing

#### *N. lactamica* identification

Working in a class 2 microbiological safety cabinet in a Containment Level 2 laboratory, all respiratory samples will be suspended in 1 mL storage medium (10% glycerol in 0.1% diethylpyrocarbonate (DEPC)-treated water). Agar selective for *N. lactamica* (GC agar supplemented with 5-bromo-4-chloro-3-indolyl-β-galactopyranoside (X-gal); Thermo Fisher Scientific, Basingstoke, UK) will be inoculated with sample solution, and all remaining sample solution will be split into 200 µL aliquots for storage in a secure, temperature-monitored −80°C freezer. Following 24–48 hours incubation, colonies with typical *N. lactamica* morphology (blue on GC X-gal agar) will undergo identification by oxidase reaction, Gram stain, microscopy and analytical profile index (API-NH, bioMérieux, Lyon, France) or matrix-assisted laser desorption/ionisation time-of-flight (MALDI-TOF; Bruker, Coventry, UK). *N. lactamica* density will be quantified and isolates will be stored at −80°C. Breastmilk will also be plated onto selective agar to examine for evidence of *N. lactamica*, and residual samples will be stored at −80°C for microbiome analysis.

#### *N. lactamica* Y92-1009 strain-specific PCR

We have identified two chromosomal loci present in *N. lactamica* strain Y92-1009 that, when amplified in conventional multiplex PCR and analysed by agarose gel electrophoresis, produce amplicons with a characteristic band pattern.^18^ Using the same multiplex PCR on isolates of naturally circulating strains of *N. lactamica*, this band pattern has not been reproduced. A third locus, present in all known strains of *N. lactamica*, is included to differentiate between PCR failure (no bands produced) and any non-Y92-1009 strain of *N. lactamica* (band produced, but Y92-1009-specific bands pattern not present). This PCR assay has been validated using genomic DNA and boiled bacterial lysate as a template, with an optimum annealing temperature 65°C and extension time 15 s (unpublished data).

### Microbiome analysis

Paired mother–infant frozen sample aliquots will be transported to the University of Edinburgh Centre for Inflammation Research for 16S rRNA gene sequencing.^6^ Resulting sequence reads will undergo taxonomic classification to compare mothers and infants, and (assuming some neonates become colonised with *N. lactamica*) colonised and uncolonised infants, across different sample niches and study time points.

### *N. lactamica* sequencing

If any neonates become colonised with *N. lactamica*, paired mother–infant *N. lactamica* isolates will undergo whole genome sequencing to assess for differences in *N. lactamica* microevolution in mother–infant pairs. Resulting sequences will be mapped to a closed *N. lactamica* Y92-1009 reference genome for comparison.

### Sample size

To our knowledge, this proof-of-concept represents the first respiratory controlled human infection study in pregnancy. As such, it is not possible to accurately define the sample size needed to conclusively rule out induced horizontal transfer of *N. lactamica*. A pragmatic sample size of 20 inoculated volunteers has been selected: based on our earlier work, *N. lactamica* colonisation is expected in 18 (90%) of volunteers inoculated with 10^5^ CFU *N*. *lactamica*. This sample would therefore fail to detect horizontal transfer only if it occurs in less than 1 in 18 infants (<6%), in which case it would be impractical and even unethical to pursue horizontal *N. lactamica* controlled human infection as a method of studying and manipulating infant commensalisation. By 1 month of age, 2.3% of infants naturally carry *N. lactamica*.^17^ Based on a plot of lower confidence limits against observed infant *N. lactamica* colonisation for a sample of 18 experimentally-colonised volunteers, infant *N. lactamica* colonisation greater than 22% (95% CI (2.3% to 41.7%)) would demonstrate that inoculation-induced carriage exceeds natural *N. lactamica* carriage (figure 2).

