### *N. lactamica* inoculum

Vials of lyophilised (freeze-dried) *N. lactamica* (LyoNlac) will be produced and stored under Good Manufacturing Practice (GMP)-like standards at the University of Southampton. The strain used for lyophilisation (Y92-1009, sequence type 3493, clonal complex 613) originates from the current GMP-compliant pharmaceutical manufacturing facilities at Public Health England (Porton Down, UK). Lyophilised inoculum stocks can be stored at 4°C (unlike frozen stocks requiring storage at −80°C). LyoNlac will be reconstituted in phosphate buffered saline and diluted to a concentration of 10^5^ CFU/mL for inoculation. In our previous work, this dose resulted in *N. lactamica* colonisation in 100% of 10 adults receiving lyophilised inoculum and 85% of 20 adults using frozen inoculum (ie, 90% overall). The inoculum will be administered immediately following reconstitution and serial dilution, and after no more than 30 min delay; recovery of viable bacteria remains over 70% after 30 min incubation in room air (unpublished data).

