### Statistical analysis

The primary endpoint will be expressed as a proportion N/M, where:

M=Number of mothers colonised with *N. lactamica*.N=Number of neonates (aged 0–31 days) colonised with the same strain of *N. lactamica* as their own mother.‘Colonised’=evidence of *N. lactamica* by culture of upper respiratory swabs (using selective media and confirmation by API or MALDI-TOF) on at least one visit.‘Same strain’=confirmed using Y92-specific *N. lactamica* PCR for inoculated volunteers, or whole genome sequencing for volunteers already naturally carrying *N. lactamica* at screening.

Subgroup analysis will be performed, to compare inoculated mother–infant pairs with naturally colonised mother–infant pairs, and to compare pairs where the mother or infant received antibiotics with pairs not receiving antibiotics.

Specific bioinformatic analysis strategies will depend on the quantity and quality of genomic data produced during the study, and on the rates of *N. lactamica* colonisation observed. Broadly speaking, microbiome bioinformatic pipelines (eg, QIIME2 and R packages) will be used to perform taxonomic classification, calculation of alpha and beta diversity and data visualisation.

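### With 18 colonised mothers, a true transfer rate of 6% would go unseen about a third of the time, so 1 in 18 is not a guaranteed detection limit

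*Protocol article*

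**What the plan says.** All of the relevant text is in the protocol article, mainly under Sample size.

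- The size is presented as a practical choice: "A pragmatic sample size of 20 inoculated volunteers has been selected".
- The denominator for transfer follows from the assumed maternal take: "colonisation is expected in 18 (90%) of volunteers inoculated with" the study dose. The section on the inoculum gives the source of the 90%: "100% of 10 adults receiving lyophilised inoculum and 85% of 20 adults using frozen inoculum (ie, 90% overall").
- The detection claim is then drawn from these figures: "This sample would therefore fail to detect horizontal transfer only if it occurs in less than 1 in 18 infants (<6" per cent).
- The same sentence attaches a consequence to a rate that low: "in which case it would be impractical and even unethical to pursue horizontal" controlled infection by this route.
- Two sentences before the claim stands a caveat: "it is not possible to accurately define the sample size needed to conclusively rule out induced horizontal transfer".
- A second criterion follows, on exceeding natural carriage of 2.3%: observed infant colonisation above "22% (95% CI (2.3% to 41.7" per cent).

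Under Statistical analysis, "The primary endpoint will be expressed as a proportion N/M", where M counts colonised mothers and N counts neonates carrying their own mother's strain. No detection probability or confidence level is attached to the 1-in-18 statement.

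**The concern.** The words *only if* say that the study cannot miss transfer occurring at 6% or more. That confuses two quantities. With 18 infants the observed proportion can be 0, 1/18, 2/18 and so on, so 1/18 is the smallest non-zero result available. The true rate at which at least one transfer becomes likely depends on sampling variation, which the sentence leaves out.

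What is at stake is the reading of a null primary result. Whether transfer occurs at all is the aim given under Rationale for this study, and it is what N/M measures. If failure to detect could arise only when the true rate is below 6%, then 0/18 would imply a rate below 6%. The second half of the sentence would then make that a reason not to pursue the method. Neither step is sound if zero events are common at rates well above 6%.

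**Working it through.** **Inputs.** 20 inoculated women, 90% expected maternal colonisation and hence 18 colonised mothers (Sample size); up to 10 additional volunteers to offset antibiotic use (end of the Sample size section).

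**The plan's own figures.** The 90% is (10 + 0.85 × 20)/30 = 27/30. Then 0.90 × 20 = 18, and 1/18 = 5.56%, printed as <6%. The arithmetic reproduces; the interpretation does not.

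**Chance of seeing no transfer.** If each infant of a colonised mother independently acquires the strain with probability *p*, then P(0 of 18) = (1 − *p*)^18.

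| True rate *p* | P(0 of 18) | P(at least 1) |
|---|---|---|
| 1/18 = 5.56% | 35.7% | 64.3% |
| 6% | 32.8% | 67.2% |
| 8% | 22.3% | 77.7% |
| 10% | 15.0% | 85.0% |
| 12% | 10.0% | 90.0% |
| 15% | 5.4% | 94.6% |
| 20% | 1.8% | 98.2% |

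The sentence in the protocol requires the middle column to be zero from about 6% upwards.

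**Rate needed for a given chance of detection.** Solving 1 − (1 − *p*)^18 = *d* gives *p* = 1 − (1 − *d*)^(1/18):

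- *d* = 80%: 1 − 0.20^(1/18) = 8.6%
- *d* = 90%: 1 − 0.10^(1/18) = 12.0%
- *d* = 95%: 1 − 0.05^(1/18) = 15.3%

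**What 0/18 would exclude.** The one-sided 95% upper limit is 1 − 0.05^(1/18) = 15.3%. The two-sided exact (Clopper–Pearson) 95% upper limit is 1 − 0.025^(1/18) = 18.5%.

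**Sensitivity to the denominator, all at *p* = 6%.**

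- Maternal take random at 90% of 20: (1 − 0.9 × 0.06)^20 = 32.9%.
- Only 16 mothers colonised: 0.94^16 = 37.2%.
- All 10 optional volunteers added, 0.90 × 30 = 27 colonised: 0.94^27 = 18.8%.

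**Colonised mothers needed at 6%.** ln(0.05)/ln(0.94) = 48.4, so 49 for 95% detection; ln(0.20)/ln(0.94) = 26.01, so 27 for 80%. These numbers show the scale of the gap; they are not a proposal to enlarge the study.

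**The case against.** There are four serious points on the other side.

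1. **The section disclaims a conclusive negative.** It says that the size needed to rule out transfer cannot be accurately defined, and it calls its own size pragmatic. This shows awareness of the limitation and lowers the risk of over-reading. It does not correct the later sentence, however: the caveat and the *only if* claim conflict, and the claim is the one that carries a figure.

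2. **The sentence may refer to the observed proportion.** It would then be true but empty, since it says that no transfer is seen when fewer than one transfer is seen. It could not support the clause on whether the method is worth pursuing, which needs the population rate.

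3. **A reader might infer that the plan commits to abandoning the approach after 0/18, or to reporting the rate as below 6%.** The documents do not say this. The clause attaches to a low rate of transfer, not to an observed zero. There is no formal stopping or futility rule, and the analysis section simply reports N/M. The link from a null result to giving up the method is an implication of the wording. This objection stands, and the point is limited accordingly.

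4. **A reader might also take the 1-in-18 claim as the whole justification of the sample size.** It is not. The 22% criterion against natural carriage is a separate basis. The 1-in-18 claim is the only one about detecting any transfer at all.

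The exploratory nature of the study justifies a pragmatic size, but not an incorrect account of what that size can show. Nor is this a detail that could be left to an analysis plan, because it is a false statement in the published text.

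**Conclusion.** The detection claim is wrong as written. At the very threshold that it names, the planned sample would show no transfer roughly one time in three (36% at 1/18, 33% at 6%). Zero transfers among 18 would be compatible with true rates up to about 15% (one-sided 95%) or 18.5% (two-sided 95%), some three times the stated limit. Using every optional volunteer reduces the miss probability at 6% to about 19%, not to zero.

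The calculation assumes independent pairs, one common transfer rate and perfect sensitivity of sampling and culture. Imperfect sensitivity would raise every miss probability. The one-third figure is for the base case of 18 colonised mothers and changes little when maternal take is allowed to vary.

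The consequence is confined to how a null primary result is interpreted. The design, the endpoint and the 22% criterion are untouched.

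**What to change.** Replace the detection sentence with wording such as:

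> With 18 colonised mothers the study has about a 67% chance of observing at least one transfer if the true rate is 6%, and 95% if it is about 15.3% or more. A result of 0/18 would exclude rates above about 15% (one-sided 95%) or 18.5% (two-sided 95%), not above 6%.

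Then either remove the inference that the method would not be worth pursuing, or restate it against that upper limit. This would also bring the sentence into line with the section's own caveat.

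The cost is a short edit to the Sample size section and a less favourable stated sensitivity. No additional participants, procedures or analyses are required. The correction should be in place before any null result is interpreted.

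### The 2.3% benchmark behind the 22% criterion is natural carriage of any *N. lactamica* strain, but the primary proportion N/M counts only infants carrying their own mother's strain

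*Protocol article*

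**What the plan says.** **Sample size.** Natural carriage is given at species level: "By 1 month of age, 2.3% of infants naturally carry" *N. lactamica*. Maternal "colonisation is expected in 18 (90%) of volunteers inoculated with" the study dose. From a plot of lower confidence limits "for a sample of 18 experimentally-colonised volunteers", the section concludes that infant "colonisation greater than 22% (95% CI (2.3% to 41.7%)) would demonstrate that inoculation-induced carriage exceeds natural" carriage. A little earlier it says that the sample would miss horizontal transfer only if transfer occurred in fewer than 1 in 18 infants.

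**Statistical analysis.** The primary endpoint is a proportion N/M. M is the number of colonised mothers. The numerator is defined as "N=Number of neonates (aged 0–31 days) colonised with the same strain of" *N. lactamica* as their own mother. For inoculated volunteers the match is "confirmed using Y92-specific" PCR; for naturally colonised volunteers it is whole genome sequencing.

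**Strain-specific PCR.** In naturally circulating isolates, "this band pattern has not been reproduced". The number of isolates tested is not given. A third locus identifies other strains of the species ("band produced, but Y92-1009-specific bands pattern not present").

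**Table 1.** The primary endpoint is neonatal *N. lactamica* by selective culture, with no strain condition. Y92-1009 by strain-specific PCR is listed as secondary.

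**The concern.** An infant who picks up a wild strain from a sibling contributes to a figure such as 2.3%, but cannot enter N for an inoculated pair. Strain typing has already taken the natural background out of the numerator, and the benchmark puts it back. The study hypothesis is that transmission from experimentally colonised women to their infants occurs. A Y92-confirmed infant bears on that directly, whatever the frequency of other strains.

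What is at stake is the reading of a small positive result. If 1, 2 or 3 infants are confirmed, one statement in the Sample size section says that transfer has been detected, while the 22% criterion is missed. The protocol does not say which statement goes with which endpoint, and Table 1 and the Statistical analysis section disagree on which endpoint is primary.

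**Working it through.** **Inputs.** 18 colonised mothers, 2.3% natural carriage and the 22% criterion with interval 2.3% to 41.7% (Sample size); same-strain numerator (Statistical analysis); Y92-1009 pattern unobserved in natural isolates (strain-specific PCR). True transfer rates of 10%, 15% and 20% are assumptions, chosen to span a plausible range.

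**1. Reproduce the stated figure.** A Wald interval is p ± 1.96 × √(p(1−p)/d). With p = 0.22 and d = 17 (that is, n − 1):

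0.22 ± 1.96 × √(0.22 × 0.78 / 17) = 0.22 ± 0.197, or 2.3% to 41.7%.

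This matches. With d = 18 the interval is 2.9% to 41.1%. The figure is reproducible, so the point concerns the comparator.

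**2. Turn the criterion into counts.** 3/18 = 16.7% misses 22%; 4/18 = 22.2% meets it. The criterion therefore needs 4 infants.

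**3. Exact (Clopper-Pearson) 95% intervals with 18 mothers.**

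| Infants | Proportion | Exact 95% CI |
|---|---|---|
| 1/18 | 5.6% | 0.14% to 27.3% |
| 2/18 | 11.1% | 1.4% to 34.7% |
| 3/18 | 16.7% | 3.6% to 41.4% |
| 4/18 | 22.2% | 6.4% to 47.6% |

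Against 2.3%, an exact interval is already clear at 3/18: P(X ≥ 3 | 2.3%) = 0.0077, while P(X ≥ 2 | 2.3%) = 0.063. So even for an any-strain endpoint, where the benchmark fits, the 22% criterion asks for one infant more than an exact interval does.

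**4. Chance of the ambiguous result.** With X ~ Binomial(18, p), P(1 ≤ X ≤ 3) = P(X ≥ 1) − P(X ≥ 4).

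| True rate | P(X ≥ 1) | P(X ≥ 4) | P(1 to 3) |
|---|---|---|---|
| 10% | 0.850 | 0.098 | 0.752 |
| 15% | 0.946 | 0.280 | 0.667 |
| 20% | 0.982 | 0.499 | 0.483 |

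**5. How far the Y92 background can be taken as zero.** The protocol gives no nonzero figure, so the following is an assumed range. At backgrounds of 0.05%, 0.1%, 0.2% and 0.5%, the chance of at least one background Y92 infant in 18 is 0.9%, 1.8%, 3.5% and 8.6%. The chance of two or more is at most 0.4% throughout. A single confirmed infant is strong evidence if the background is very low, and two are strong evidence across the whole range.

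**The case against.** The strongest reply is that the 22% figure is not a test. It appears only under Sample size; the Statistical analysis section reports N/M and names no null value. A reader might infer that the trial will formally test N/M against 2.3% and so answers the wrong question. The documents do not support that: 22% is a planning criterion.

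A reader might also infer that 1 to 3 confirmed infants would be reported as a failed study. That too goes beyond the text, because the Sample size section already treats about 1 in 18 as detecting transfer. The probabilities in step 4 are therefore not probabilities of a wrong conclusion. They are probabilities of showing transfer while missing the only numerical criterion given.

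Asking whether induced Y92 carriage is more frequent than natural carriage of the species can also be a deliberate and useful description, and against Table 1's any-strain primary endpoint 2.3% is the right kind of comparator. Both points stand. They do not remove the mismatch with N/M, and the second adds a conflict over which endpoint is primary.

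Three further inferences should be resisted:
- **The Y92 background is proven zero.** The text says only that the pattern was not reproduced, in an unstated number of isolates.
- **2.3% is too low because infants are sampled at three visits.** The wording is compatible with a cumulative figure, which would match positivity at any visit; the document does not say.
- **The source of 2.3% is wrong because the same reference number supports the adult inoculation results.** One reference can support several facts, and the source is not available here.

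**Conclusion.** The point holds as a mismatch between benchmark and numerator. The 2.3%/22% criterion belongs with any-strain infant carriage, as in Table 1, and does not fit same-strain N/M in inoculated pairs as defined under Statistical analysis. The direction is conservative: the criterion asks for 4/18 where the protocol's own reading of detection is about 1/18, and it does not inflate false claims of transfer. The ambiguous outcome is the likeliest one at true rates of 10% and 15% (75% and 67%) and close to half at 20% (48%).

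These figures assume exactly 18 colonised inoculated mothers, independent mother–infant pairs and a common transfer rate. Reading a single Y92-confirmed infant as transfer also rests on a very low natural background of that strain, which the protocol supports but does not quantify. None of this carries over to naturally colonised pairs, whose strain match is made by sequencing.

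**What to change.** 1. Reconcile Table 1 with the Statistical analysis section and state which endpoint is primary: any-strain culture or the same-strain proportion.
2. For Y92-confirmed N/M in inoculated pairs, report the proportion with an exact 95% interval and read it as evidence of transfer, without the 2.3%/22% criterion. State that the natural background of Y92-1009 is unobserved rather than proven zero, and give the number of isolates behind that statement. Tabulate naturally colonised pairs separately.
3. Use the comparison with 2.3% only for any-strain infant carriage, with an exact interval (3/18 has a lower limit of 3.6%).
4. State whether 2.3% is cumulative to 1 month or a point prevalence, and choose the visit window for the any-strain comparison to match.

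The cost is a few sentences and one additional tabulation. No new samples, visits or participants are needed, since culture and strain-specific PCR are already planned.

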### Controlled human infection with *Neisseria lactamica*

Unlike probiotic studies (which often employ proprietary food supplements with uncontrolled concentrations of bacteria), controlled human infection offers a robust model for studying the impact of a defined bacterial inoculum on a human host. Our research group has previously developed a safe and reliable controlled human infection model using nasal inoculation with 10^4^–10^5^ colony-forming units (CFU) *N. lactamica* strain Y92-1009 in healthy adults.^17 18^ In randomised blinded placebo-controlled studies, we have characterised *N. lactamica* colonisation density, duration, cellular and humoral immune responses, and genomic microevolution,^19^ observing colonisation rates of up to 85% and no serious adverse reactions following over 400 inoculations.

*N. lactamica* is a common non-capsulated pharyngeal commensal that does not cause invasive disease in immunocompetent hosts. Colonisation peaks at over 40% in 1–2 year-old children,^20^ before falling to less than 10% in adulthood,^21^ and *N. lactamica* carriage correlates inversely with *N. meningitidis* colonisation.^22^ Indeed, *N. lactamica* controlled human infection in healthy adults reduced naturally-acquired *N. meningitidis* carriage from 18% to 8% (both by displacing existing colonisation and preventing new acquisition), exceeding the typical impact of glycoconjugate ACWY vaccination.^17^ This displacement effect is not specific to a particular serogroup, unlike available glycoconjugate meningococcal vaccines. Furthermore, natural colonisation with *N. lactamica* has been observed to correlate inversely with invasive meningococcal disease.^21^

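### The 22% benchmark for exceeding natural carriage rests on a normal approximation unsuited to 18 pairs; it asks for 4 infants where an exact interval needs 3

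*Protocol article*

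**What the plan says.** All of this is in the Sample size section of the protocol article unless another section is named.

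- Size: "A pragmatic sample size of 20 inoculated volunteers has been selected".
- Expected denominator: "colonisation is expected in 18 (90%) of volunteers inoculated with" the planned inoculum.
- Reference rate: "By 1 month of age, 2.3% of infants naturally carry" the organism.
- Source of the benchmark: "Based on a plot of lower confidence limits against observed infant" colonisation, "for a sample of 18 experimentally-colonised volunteers". The interval method is not named, and the figure cannot be seen in the text at hand.
- Benchmark: infant "colonisation greater than 22% (95% CI (2.3% to 41.7%)) would demonstrate that inoculation-induced carriage exceeds natural" carriage.

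The Statistical analysis section expresses the primary endpoint as a proportion N/M. M is the number of colonised mothers and N the number of neonates carrying the same strain as their own mother. It does not repeat the 22%.

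**The concern.** The benchmark is the observed rate at which the lower 95% limit reaches 2.3%. Where that point falls depends on the interval method, and with 18 pairs the methods differ by whole infants. A symmetric interval around 22% with so few events is a sign that a large-sample formula was used where it does not work well.

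This is the only figure the article prints for judging whether carriage after inoculation exceeds natural carriage. If it is set too high, a result that an exact analysis would call an excess, such as 3 of 18, may be read as inconclusive. A percentage fixed at one denominator also shifts in whole infants as the number of colonised mothers varies, and that number is not known in advance.

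**Working it through.** **Inputs.** From the Sample size section: 18 colonised mothers (90% of 20 inoculated), natural carriage 2.3% (treated as fixed), printed benchmark 22% with 95% CI 2.3% to 41.7%. The true rates used in step 4 are assumptions.

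**1. Reproduce the printed interval.** Wald interval: p ± 1.96 × √(p(1−p)/d).

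- d = 18: 0.22 ± 1.96 × √(0.22 × 0.78/18) = 0.22 ± 0.191, or 2.9% to 41.1%. No match.
- d = 17: 0.22 ± 1.96 × √(0.22 × 0.78/17) = 0.22 ± 0.197, or 2.3% to 41.7%. Match.

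A divisor of 17 is either n = 17 or n = 18 with the n−1 form of the variance; the two are algebraically the same. The divisor does not alter the count. The lower limit meets 2.3% at 21.2% with d = 18 and at 22.0% with d = 17. Since 3/18 = 16.7% and 4/18 = 22.2%, both forms need 4 infants.

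**2. The approximation at the neighbouring count.** For 3/18, Wald with d = 18 gives 0.1667 ± 0.1722, or −0.6% to 33.9%. A negative limit is impossible for a proportion.

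**3. Exact intervals.** The Clopper-Pearson lower limit is the 2.5% quantile of Beta(x, n−x+1); the upper limit is the 97.5% quantile of Beta(x+1, n−x). The tail is P(X ≥ x) for X ~ Binomial(18, 0.023).

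| Infants | Observed | Exact 95% CI | One-sided tail at 2.3% |
|---|---|---|---|
| 2/18 | 11.1% | 1.4% to 34.7% | 0.063 |
| 3/18 | 16.7% | 3.6% to 41.4% | 0.0077 |
| 4/18 | 22.2% | 6.4% to 47.6% | 0.0007 |

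The tail at 3 is 1 − (0.6578 + 0.2787 + 0.0558) = 0.0077. The exact interval first excludes 2.3% at 3/18.

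**4. What the extra infant costs.** P(X ≥ 4) against P(X ≥ 3) for X ~ Binomial(18, true rate):

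| True rate | At least 4/18 | At least 3/18 |
|---|---|---|
| 2.3% (false positive) | 0.07% | 0.77% |
| 15% | 28% | 52% |
| 20% | 50% | 73% |
| 25% | 69% | 86% |

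Both false-positive rates are well under 2.5%.

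**5. Other denominators.** If M ~ Binomial(20, 0.9):

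- P(M = 18) = 190 × 0.9^18 × 0.1^2 = 0.29
- P(M = 19) = 20 × 0.9^19 × 0.1 = 0.27
- P(M = 20) = 0.9^20 = 0.12

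So M is 19 or 20 with probability of about 0.39. At M = 19, 4/19 = 21.1%; at M = 20, 4/20 = 20.0%. Neither exceeds 22%, so 5 infants are needed. The exact bar is still 3: 3/20 gives 3.2% to 37.9%. It remains 3 for every M from 15 to 27.

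**The case against.** **The sentence is not false.** It gives a sufficient condition, and more than 22% of 18 would show an excess under the exact method too: 4/18 has a lower limit of 6.4%. This stands. The error is on the cautious side and cannot by itself produce a false claim. What does not hold is 22% as the point where the lower limit meets natural carriage.

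**A reader might infer that the interval was computed for the wrong number of mothers**, perhaps 17 as 85% of 20, since the Introduction reports "observing colonisation rates of up to 85" per cent. The documents do not support this. The same figures follow exactly from 18 with an n−1 variance, the article explains how it arrives at 90%, and the count is 4/18 either way.

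**A reader might infer that 3/18 would be declared no better than natural carriage.** No section says so. The Statistical analysis section sets no test or cut-off, and 22% appears only in the sample-size rationale of a study whose size is called pragmatic. The probabilities in step 4 therefore describe the benchmark if it is used to judge the result; they are not the properties of a stated decision rule. Nor is 22% the section's only quantitative threshold: it also names a transfer rate below 1 in 18 at which the approach would not be worth pursuing.

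**One infant too many is relative to Clopper-Pearson.** This also stands. Wilson (3.1%) and Jeffreys (2.4%) lower limits already exceed 2.3% at 2/18, where the exact tail is 0.063. Those methods put the bar lower still, so they give no support to 22%.

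**Planning at the expected denominator is ordinary practice.** True, and the article says its plot is for 18. The difficulty arises only if the percentage is carried over to another M.

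**Conclusion.** The concern holds as a point about method and calibration. The benchmark comes from a normal-approximation interval that is unsuitable for 3 or 4 events in 18. It is one infant stricter than an exact 95% criterion at M = 18 and, read literally, two infants stricter at M = 19 or 20. At a true rate of 20% with 18 pairs, the chance of clearing it falls from 73% to 50%, with no needed gain in protection against a false positive.

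The conclusion rests on three assumptions: the 2.3% reference is taken as known without error, the exact two-sided 95% Clopper-Pearson interval is the standard of comparison, and pairs are independent with a common transfer rate. The likelihood of each M also takes the 90% colonisation rate as given.

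Severity is should-fix. The sample size, data collection and endpoint definition are unaffected, but a printed threshold ought to be right before it is used to interpret the result.

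**What to change.** Before results are seen:

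- Restate the benchmark as follows: the lower limit of the exact (Clopper-Pearson) two-sided 95% interval for the observed N/M among inoculated pairs exceeds 2.3%. Restricting it to inoculated pairs matters because the endpoint's M, as defined, can also include naturally colonised mothers.
- Replace 22% (2.3% to 41.7%) with the planning example 3/18 (16.7%, 95% CI 3.6% to 41.4%), and say that the limit is recomputed for the M observed.
- Name the interval method, and redraw figure 2 with exact limits if it does not already use them.

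The cost is a few sentences and at most one figure, with no extra participants or samples. Timing matters, because lowering the bar after the data are known would look driven by the result.
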